### 7.2.3 Supportive Analyses of the Primary Outcome Measure

The primary outcome will be analyzed as above for the PP population.

Given the relative advantages of Generalized Estimating Equations and generalized linear mixed models (GLMM), sensitivity analyses will compare treatments using a logistic regression with SAS PROC GLMMIX, with a random effect for subject.

```
proc glimmix data = primdat;
  class engage site site2 (ref = '02156') patid trt (ref = 'SL-BUP')
    visno (ref = 'C07') gender (ref = '1') race_cat (ref = '1')
    ethnic_cat (ref = '0') insurance_rand (ref = '1');
  model engage (event = '1') = trt visno trt * visno site2 age gender
    race_cat ethnic_cat insurance_rand /*prior_engagement*/ /
    dist = bin link = logit;
  random _residual_ / subject = patid type = cs;
  weight wgt;
  lsmeans trt * visno / pdiff oddsratio cl;
run;
```

Additional sensitivity analyses may be conducted to evaluate the effect of changes in eligibility criteria.

The supportive analyses of the primary outcome will be analyzed for the ITT and PP populations.

Subgroup analyses for sex, race, ethnicity, and age will be performed as required by the NIH (NIH, 2016). The proportions and confidence intervals for each of the primary outcome measures will be estimated in the following subgroups for the ITT population:

- 1) Males and females

- 2) Black, White, and all other races
- 3) Hispanic and non-Hispanic participants
- 4) Participants older than the median age and those equal to or younger than the median age.

The primary analysis will be re-run with a covariate for the subgroup and the interaction between the subgroup and treatment. Estimate statements will be used to determine the treatment effects and associated confidence intervals for each group.

Additional subgroups of interest include the following:

- 1) Housing status at baseline (unstable housing in last 12 months (DM1.DMNIGHT = yes versus no); currently in unstable housing (DM1.DMLIVING = yes versus no))
- 2) Fentanyl positive (UDS.UDFEN1 = positive) and fentanyl negative (UDS.UDFEN1 = negative) from baseline UDS
- 3) Stimulant positive (UDS.UDAMP1 = positive or UDS.UDMET1 = positive) and stimulant negative (UDS.UDAMP1 = positive and UDS.UDMET1 = positive) from baseline UDS
- 4) Treatment seeking at the index ED visit (EDR.ERPRBTYP = 'Seeking referral for OUD treatment' versus other reasons)
- 5) Overdose at the index ED visit (EDR.ERPRBTYP = 'Overdose' versus other reasons)

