### **8.6.4 Urine Drug Screen (Toxicology Testing)**

Urine testing will be performed for the presence of the following drugs: opioids, oxycodone, benzodiazepines, cocaine, methamphetamine, amphetamine, phencyclidine, ecstasy (MDMA), marijuana (THC), barbiturate, methadone, buprenorphine, and fentanyl. The urine drug screen is collected during the screening phase of the initial ED visit. The fentanyl point of care test strip is being used for research purposes only. Urine testing supplies (e.g., dip stick) will be provided to the sites. In addition, a sample of urine will be collected on each enrolled participant and frozen for future testing for fentanyl (and analogues) with a gold standard method (e.g., Gas Chromatography/Mass Spectroscopy) coordinated by Emmes.

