### 8.7.7 Timeline Follow-Back (TLFB)

The Timeline Follow-back procedure, will be used to elicit the patient participant's self-reported use, quantity, and route of administration of opioids, marijuana, stimulants, benzodiazepines and alcohol. At enrollment, substance use is reported by the patient participant for the 7-day period prior to informed consent. At the 7-day follow-up assessment, substance use is reported for the 7 days following the ED Index Visit (Day 0). At the 30-day follow-up assessment, substance use is reported for the 7 days prior to study day 30.

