### 12.3 Sample Size Justification for Evaluation of Effectiveness

For the comparison of XR vs. Standard SL-BUP, the primary effectiveness outcome will be engagement in formal addiction treatment at 7 days, classified as engaged or not engaged based on verification with the treatment provider. A sample size of 850 per group is required to ensure 90% power at the 2-sided 0.05 significance level to detect a difference in the proportion engaged of 8% between SL and XR-BUP (i.e., 45% engaged in SL vs. 53% engaged in XR-BUP). We will enroll approximately 2000 patients to accommodate a 15% dropout. Figure 6 below shows the sensitivity of the power of the study given variations in the proportions of those engaged in treatment. Regardless of the proportion engaged in treatment in the SL group, our sample size will provide > 90% to detect improvements for the XR group of 8% and > 80% to detect improvements of 7%. This sample size will also provide sufficient power to detect differences in notable subgroups (treatment seeking, rural/urban, insurance Y/N).

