#### **9.2 RCT Component**

All p-values will be assessed at the 0.05 level. There is a single primary outcome, and there are no plans to adjust supportive or secondary analyses for multiplicity.

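### The RCT stimulant subgroup in SAP 7.2.3 has a negative group nested inside its positive group, and its positive group leaves out the cocaine screen

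*Combined protocol and SAP*

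**What the plan says.** SAP 7.2.3 lists additional subgroups of interest for the RCT primary outcome. The third is stimulant status on the baseline urine drug screen. The positive group is "Stimulant positive (UDS.UDAMP1 = positive or UDS.UDMET1 = positive", and the other group is "stimulant negative (UDS.UDAMP1 = positive and UDS.UDMET1 = positive) from baseline UDS".

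The model for the subgroups is set out in the same section: "The primary analysis will be re-run with a covariate for the subgroup and the interaction between the subgroup and treatment". Treatment effects and confidence intervals are then estimated for each group.

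Protocol 8.6.4 gives the RCT urine panel, which includes "opioids, oxycodone, benzodiazepines, cocaine, methamphetamine, amphetamine, phencyclidine, ecstasy (MDMA". Cocaine is therefore tested at the same visit and on the same panel as the two screens that the SAP uses.

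Neither document defines *stimulant* for this analysis. Protocol 8.7.7 names it as a self-report class, "opioids, marijuana, stimulants, benzodiazepines and alcohol", without listing the drugs in it.

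**The concern.** A subgroup comparison needs two groups that do not overlap and that together cover the participants with a result. The rule as written gives neither. Its reference group consists of people positive on both screens, so the analysis would contain no group free of amphetamine-type drugs.

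The line cannot be run sensibly, so someone will edit it. The obvious edit changes *positive* to *negative* in the second half. That cures the overlap but exposes the second fault: participants positive for cocaine only, among the three screens, would move into a group labelled stimulant negative. The effect reported for that group would then be partly an effect in users of a drug that many readers would call a stimulant. If those users respond like the positive group, the difference between the two subgroup effects would be understated.

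**Working it through.** **Inputs.** The two definitions are from SAP 7.2.3 and the panel contents from protocol 8.6.4. I take UDMET1 to be methamphetamine. The documents do not spell this out, but methadone-positive patients are excluded from the RCT (protocol 8.3.2, SAP 2.3.2.2), so a methadone reading would make no sense here. The plan gives no figure for this subgroup, so there is none to reproduce.

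**Step 1: classify every result pattern.** Three binary screens give 2 × 2 × 2 = 8 patterns. Each of the first three rows covers two patterns, cocaine positive and cocaine negative.

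| Amphetamine | Methamphetamine | Cocaine | SAP positive | SAP negative, as written | Negative, if both must be negative | Three-screen rule |
|---|---|---|---|---|---|---|
| + | + | + or − | yes | yes | no | positive |
| + | − | + or − | yes | no | no | positive |
| − | + | + or − | yes | no | no | positive |
| − | − | + | no | no | yes | positive |
| − | − | − | no | no | yes | negative |

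Under the rule as written:
- 6 of 8 patterns are positive.
- 2 of those 6 are also negative.
- The remaining 8 − 6 = 2 patterns are in neither group.

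The cocaine-only pattern is one of the two in neither group. At present it is not in the reference group and cannot dilute it.

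Under the simple repair (both screens negative), the overlap and the gap disappear, and the cocaine-only pattern moves into the negative group.

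Under the three-screen rule, exactly one pattern changes group relative to the simple repair: amphetamine negative, methamphetamine negative, cocaine positive. Cocaine users who also screen positive for either of the other two are in the positive group under every rule.

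**Step 2: what the simple repair could cost.** Let *c* be the share of the repaired negative group that is positive for cocaine. Let *d*₊ be the treatment effect in stimulant users and *d*₋ the effect in non-users, both as risk differences. If cocaine-only users share the effect *d*₊, the negative group shows (1 − *c*)*d*₋ + *c·d*₊. The subgroup contrast becomes

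*d*₊ − [(1 − *c*)*d*₋ + *c·d*₊] = (1 − *c*)(*d*₊ − *d*₋).

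With variance held fixed, the sample size needed to detect the contrast grows by about 1/(1 − *c*)².

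The documents give no cocaine or stimulant prevalence, so *c* is an assumed range:

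| *c* (assumed) | Contrast kept, 1 − *c* | Sample size multiplier, 1/(1 − *c*)² |
|---|---|---|
| 0.05 | 95% | 1.11 |
| 0.10 | 90% | 1.23 |
| 0.20 | 80% | 1.56 |
| 0.30 | 70% | 2.04 |
| 0.40 | 60% | 2.78 |
| 0.50 | 50% | 4.0 |

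The planned model is a logistic GEE, so on the odds-ratio scale these factors are only approximate.

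**The case against.** The case against giving this much weight has several parts.

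- **Dilution is not in the plan as written.** A reader might infer that cocaine users already contaminate the reference group. They do not: under the written rule a cocaine-only participant is in neither group. Dilution arises only if the negative rule is corrected and cocaine is left out. This part of the objection stands.
- **The omission is narrower than cocaine use as a whole.** Only participants negative on both other screens are affected. This also stands.
- **An amphetamine-type subgroup may be intended.** Nothing in the documents says that a stimulant group must include cocaine, so the restriction could be a choice. That is possible, but no reason is given and the label does not show it. The self-report classes in protocol 8.7.7 have no separate place for cocaine, which hints at a broader meaning but does not settle it. Ecstasy (MDMA) is also on the panel, so any rule has to say where its line falls.
- **The percentages rest on assumptions.** They need an assumed *c* and an assumed equal response. If cocaine-only users respond differently from amphetamine-type users, the bias could run the other way, and pooling them into the positive group could blur that group instead. This stands.
- **The stakes are low.** This is a supportive subgroup, and the SAP says "there are no plans to adjust supportive or secondary analyses for multiplicity". It is not among the "notable subgroups (treatment seeking, rural/urban, insurance Y/N" for which protocol 12.3 asserts power, nor among the effect modifiers named in protocol 12.6.5. SAP 7.2.6 separately plans to examine comorbid substance use.

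None of this rescues the negative definition, which contradicts its own label.

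**Conclusion.** Two faults hold. The stimulant-negative definition is a plain error: it selects a subset of the positive group and leaves everyone negative on both screens unclassified, so the subgroup cannot be used as written. The stimulant-positive definition leaves out a cocaine result that is collected at baseline, so participants positive for cocaine alone among the three screens are not counted as stimulant positive, and no reason is given.

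The first fault rests only on the text and on reading UDMET1 as methamphetamine. Any harm from the second is conditional: it needs the simple repair of the negative rule, and attenuation needs cocaine-only users to respond like other stimulant users. The table in the working shows a range, not an estimate; the documents do not allow the dilution to be sized. They also do not support saying that the comparison is diluted as it stands, or that misclassification differs by site.

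The effect is confined to one supportive subgroup without multiplicity adjustment. The primary analysis is unaffected, so the point is minor but worth correcting.

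**What to change.** Rewrite both halves of the definition in SAP 7.2.3 together, choosing one of two forms.

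1. **Stimulant use.** Positive: positive on any of the baseline amphetamine, methamphetamine or cocaine screens. Negative: negative on all three.
2. **Amphetamine-type use only.** Relabel the subgroup accordingly. Positive: positive on amphetamine or methamphetamine. Negative: negative on both, with cocaine-positive participants kept out of this reference group.

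Under either form, state whether the MDMA screen counts and why, and report by arm how many participants are positive for cocaine but negative on the other two screens.

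The SAP describes its RCT sections as a draft (14.3), and Exhibit 5 reserves version 4.0 for finalizing them before database lock, so that is the time for the change. The cost is one definition line and its code, on data already collected. Sample size and the primary analysis do not change.

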#### 8.4.9 Interventions: Buprenorphine Induction and Discharge Instructions

Uniform BUP induction protocols will be used:

a) Standard SL-BUP:

- i. COWS  $\geq 8$ : Patients will receive 4mg of SL-BUP for a COWS score of 8-12 (mild withdrawal). After 30-45 minutes if tolerated and no unanticipated adverse reactions, an additional 4mg can be administered for a total of 8mg in the ED. Patients presenting with moderate-severe withdrawal ( $\text{COWS} \geq 13$ ) will receive an initial dose of 8mg SL-BUP. All patients will receive a buprenorphine prescription and instructions for additional BUP doses to allow for up to a dose of 12mg if needed, and for 16mg each subsequent day until their scheduled follow up appointment for ongoing MOUD.
- ii. COWS 4-7: Patients will be provided with a uniform set of instructions to guide unobserved (home) induction. They will be prescribed doses of SL-BUP to allow them to take dose up to 12mg in the 24 hours after discharge. All patients will also receive a buprenorphine prescription for 16mg each subsequent day until their scheduled follow up appointment for ongoing MOUD.

b) XR-BUP Injection with CAM2038 24 mg: Based on published data for equivalency of 16mg of SL-BUP and experience with the phase 3 trial, patients will receive a 24mg dose of injectable CAM2038 in the ED on Day 0. The patient will remain in the ED for 2-hours post injection to observe for worsening withdrawal or precipitated withdrawal as defined below in Section 9.8.

- i. SL-BUP Rescue Dose: If patient's COWS score is  $> 12$  after XR-BUP injection, a 4-8 mg dose of SL-BUP can be administered.

Patients can receive any of the ancillary medications per standard of care for specific symptoms of withdrawal. Example includes ondansetron for nausea or acetaminophen for headache.

Discharge Instruction: Participants randomized to XR-BUP will receive a wallet card with instructions for signs and symptoms of precipitated withdrawal and advice to return to the ED for immediate evaluation for the first 24 hours post dosing if precipitated withdrawal is suspected. Each ED will have a clinician on call for the study to assist in assessment and treatment.

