#### 12.6.5 Subgroup Analyses

Subgroup analyses will be performed by estimating intervention differences in primary outcomes within subgroups. We are most interested in examining whether the impact of the intervention is modified by treatment seeking (Y/N), insurance (public, private, none), ethnicity/race and rural vs. urban. Two and 3-way interactions of intervention group, time and either treatment seeking, insurance, ethnicity/race or rural/urban status will be added to the weighted GEEs described above. We will estimate ORs and predicted probabilities of treatment engagement comparing XR to SL at each level of the subgroup variable at both 7 and 30 days. Linear contrasts will be used to determine whether the OR comparing XR to SL is modified by the subgroup variable.

In addition, if the results of the ancillary study lead to a mid-study expansion of the eligibility criteria to include those with COWS <8, we will conduct a sensitivity analysis to evaluate its impact. As above, two and 3-way interactions of intervention group, time and an indicator of low vs high COWS (i.e. COWS<8 vs COWS≥8) will be added to the weighted GEEs. Separate ORs comparing XR to SL will be estimated for COWS<8 and COWS≥8 for both 7 and 30 days.

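### SAP 7.2.3 miscodes stimulant negative, ties each Day-7 subgroup effect to Day 30, and omits the COWS, insurance and rural/urban estimates set out in protocol 12.6.5

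*Combined protocol and SAP*

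**What the plan says.** **Stimulant groups.** Among its additional subgroups, SAP 7.2.3 lists "Stimulant positive (UDS.UDAMP1 = positive or UDS.UDMET1 = positive") against "stimulant negative (UDS.UDAMP1 = positive and UDS.UDMET1 = positive) from baseline UDS". The item just before it ends with "fentanyl negative (UDS.UDFEN1 = negative) from baseline UDS".

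**Subgroup model.** The primary model in SAP 7.2.2 is one weighted GEE for engagement at Day 7 and Day 30, with `trt`, `visno` and `trt*visno`. For subgroups, SAP 7.2.3 states: "The primary analysis will be re-run with a covariate for the subgroup and the interaction between the subgroup and treatment". Protocol 12.6.5 asks for more: "Two and 3-way interactions of intervention group, time and either treatment seeking, insurance, ethnicity/race or rural/urban status will be added to the weighted GEEs", with odds ratios at each subgroup level at both visits.

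**COWS.** If eligibility is widened mid-study, protocol 12.6.5 says that "two and 3-way interactions of intervention group, time and an indicator of low vs high COWS" will be added, and that separate XR versus SL odds ratios will be estimated for COWS below 8 and for 8 or above, at both visits. The widening took place (protocol 8.10 addendum; SAP 2.2.1 and 2.3.2.1): RCT entry went from COWS of 8 or more to 4 or more. On this subject SAP 7.2.3 has only "Additional sensitivity analyses may be conducted to evaluate the effect of changes in eligibility criteria", a sentence that also stands in protocol 12.6.3.2.

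**Status.** SAP 14.3 calls the RCT analyses a first draft. Exhibit 5 reserves version 4.0 for finalizing them before database lock.

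**The concern.** The stimulant rule is written at variable level, so it could be programmed as it stands. The comparison would then set all stimulant-positive participants against a subset of themselves, with no true negatives.

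The subgroup model matters because the primary endpoint is Day 7. A single modification term shared by two visits lets Day-30 data move a subgroup result that will be reported as a Day-7 result. It can weaken a real Day-7 difference or suggest one that is absent.

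The COWS split matters because the SL-BUP comparator differs by stratum. At COWS 8 or above the first dose is given in the ED. At COWS 4-7, protocol 8.4.9 says: "Patients will be provided with a uniform set of instructions to guide unobserved (home) induction". Without stratum-specific odds ratios, a reader cannot see whether the pooled result holds against each form of SL-BUP.

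Protocol 12.3 also claims sufficient power for differences in three named subgroups: treatment seeking, rural/urban and insurance. Two of the three are absent from the SAP's list.

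**Working it through.** The plan states no figure to reproduce here. The check concerns definitions and model terms.

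**1. Stimulant coding.** The two rules applied to all four result pairs:

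| UDAMP1 / UDMET1 | Positive group | Negative group as written | Negative group if recoded |
|---|---|---|---|
| pos / pos | yes | yes | no |
| pos / neg | yes | no | no |
| neg / pos | yes | no | no |
| neg / neg | no | no | yes |

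As written, the negative group lies wholly inside the positive group, and the last row is unclassified. After recoding, the groups are exclusive and cover everyone with both results.

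**2. Subgroup model.** Take Day 7 as the reference visit and let g be the subgroup indicator (0 or 1). Under SAP 7.2.3:

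- Day-7 log odds ratio = b(trt) + g × b(trt×g)
- Day-30 log odds ratio = b(trt) + b(trt×visit) + g × b(trt×g)

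The term b(trt×g) is one parameter informed by both visits. With complete data it is roughly the average of the two visit-specific log ratios. If the ratio of subgroup odds ratios is 1.9 at Day 7 and 1.0 at Day 30, the shared value is about √(1.9 × 1.0) = 1.38.

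Simulation inputs, all assumed: 12,000 participants, two equal subgroups, no missing data (so unweighted), 45% control engagement at both visits, latent within-person correlation 0.5, exchangeable logistic GEE. Day-7 odds ratios are shown as subgroup 0 / subgroup 1.

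| Assumed modification | Day-30 truth | Day-7 truth | SAP model | Three-way model |
|---|---|---|---|---|
| Day 7 only | 1.2 / 1.2 | 1.0 / 1.9 | 1.21 / 1.56 | 1.07 / 1.77 |
| Day 30 only | 1.0 / 1.9 | 1.38 / 1.38 | 1.15 / 1.62 | 1.35 / 1.37 |
| Opposite at the two visits | 1.9 / 1.0 | 1.0 / 1.9 | 1.35 / 1.39 | 0.96 / 1.96 |

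Each row is one simulated data set, so the three-way column carries sampling error. The fair comparison is between the two models on the same data. In the first row the three-way model has a ratio of 1.65. Its square root is 1.28, and the SAP model's ratio is 1.29, as the averaging argument predicts.

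In percentage points for the first row, control odds are 0.45/0.55 = 0.818:

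- Subgroup 0: 1.21 × 0.818 = 0.990, or 49.7%, against 1.07 × 0.818 = 0.875, or 46.7%
- Subgroup 1: 1.56 × 0.818 = 1.276, or 56.1%, against 1.77 × 0.818 = 1.448, or 59.2%

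The shift is about 3 points in each subgroup, in opposite directions.

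**3. Commitments side by side.**

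| Subgroup | Protocol 12.6.5 | SAP 7.2.3 |
|---|---|---|
| Race, ethnicity | two- and three-way terms | listed; subgroup × treatment only |
| Treatment seeking | two- and three-way terms | listed; model form not clearly stated |
| Insurance, rural/urban | two- and three-way terms | absent |
| COWS below 8 vs 8 or above | two- and three-way terms, separate odds ratios at both visits | absent |
| Sex, age | not named | listed; subgroup × treatment only |
| Housing, fentanyl, stimulant, overdose | not named | listed; model form not clearly stated |

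For the RCT, baseline COWS has a place only in the baseline characteristics (SAP 5.2). It is not in Exhibit 2, the model code or the subgroup list.

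**The case against.** The other side has good points, and most of them limit the finding.

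- The stimulant line is plainly a slip. The group labels and the fentanyl coding beside it show the intent, and a careful programmer would ask. That stands, but it is a reason to correct the line, not to leave it.
- A reader might infer that the SAP cannot isolate a Day-7 effect at all. It can: `trt*visno` identifies the overall Day-7 effect. Only subgroup-specific Day-7 effects rest on equal modification at the two visits.
- If modification really is equal at both visits, the SAP model is correct and more precise. The simulated patterns are assumed, and nothing in the documents supports one over another. The 3-point shift is also close to the sampling error of a subgroup difference: with 850 per arm split in half and rates near 50%, √(2 × 0.25/425) = 3.4 points.
- Protocol 12.6.5 names the three-way form only for treatment seeking, insurance, ethnicity/race, rural/urban and COWS. For sex, age, housing, fentanyl, stimulant and overdose it is a recommendation, not a protocol requirement. The SAP's model sentence also comes before its list of additional subgroups, so its reach is unclear.
- A reader might infer that the SAP weakened a firm COWS commitment by rewording it. It did not. The optional sentence is in protocol 12.6.3.2 too. The protocol holds both a general *may* and a specific *will*, and the SAP carried over only the first. No document withdraws the second.
- Insurance is already a stratification factor and a model covariate; only its subgroup estimate is missing. ED type and patient characteristics appear in general terms among the exploratory evaluations (SAP 7.2.6).

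**Conclusion.** All three points hold for the supportive subgroup analyses. The primary ITT estimate and the overall Day-7 comparison are unaffected.

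- **Coding:** certain from the text. Every participant negative on both tests is lost, and every participant positive on both is counted twice.
- **Model:** the equal-modification constraint follows from the algebra. The size of any bias depends on the true pattern across visits, which is unknown. The simulated figures show direction and possible scale, not an expected error.
- **Missing estimates:** the protocol's condition for the COWS analysis was met, and the SAP does not put that analysis, or the insurance and rural/urban subgroups, into operation. No size can be attached, because the documents do not say how many RCT participants entered before the COWS change.

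A reader might go further and infer that leaving COWS out of the primary weight and outcome models is an error. The documents do not support that. COWS is not among the covariates named in protocol 12.6.3.2, randomization is stratified by site and insurance only, and omitting a prognostic covariate does not invalidate a randomized comparison.

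**What to change.** Before SAP version 4.0 is final:

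1. Recode stimulant negative as UDAMP1 = negative and UDMET1 = negative.
2. Add subgroup × visit and subgroup × treatment × visit to the subgroup model. Take Day-7 and Day-30 estimates from it, and state that the same form applies to every subgroup listed.
3. Write in, as planned estimates with *will*, the XR versus SL odds ratios at both visits for COWS 4-7 versus 8 or above, for insurance (public, private, none) and for rural versus urban.

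The cost is SAP wording and code. COWS, urine results and insurance are already recorded for each participant, and rural/urban is a site characteristic. The statistical price is wider intervals. With complete data at both visits, the standard error of the Day-7 interaction grows by about √(2/(1+ρ)), where ρ is the within-person correlation of the two visit-specific estimates. For an assumed ρ of 0.6 to 0.3, that is √(2/1.6) = 1.12 to √(2/1.3) = 1.24, or 12% to 24% wider.
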